### Phase IIIa: Clinical, functional, and biological evaluation of the study population

Patient selection will be followed by several data mining approaches to evaluate:

- The prognostic weight of MM and functional status in relation to death and hospitalization.- The relationship between MM, functional status, and polypharmacy in relation to the occurrence of new comorbidities.- The accuracy of several MM tools, such as the Charlson Comorbidity Index and its derivation, in the prediction of MM patterns, functional impairment, death, hospitalization, and the onset of new comorbidities.

### Phase IIIb: DNA extraction and purification

Following the selection of patients, blood and plasma samples will be collected for the determination of biomarkers. In this phase, DNA is extracted and purified from frozen buffy coat samples for each selected individual.

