The PROMOTERA study aims to identify promising biomarkers of healthspan and mortality, such as selected circulating proteins and several DNA methylation biomarkers in the plasma and blood samples of hospitalized older patients recruited by the Reportage project (Trial registration number: NCT01397682; July 19, 2011). The Reportage project is (50) an ongoing prospective observational study involving older patients consecutively admitted to acute care wards in INRCA research hospitals located in the Italian cities of Ancona, Fermo, Cosenza, and Casatenovo. The project began in September 2011 with the aim of creating a large data repository on demographics, comprehensive geriatric assessments, clinical and diagnostic information, and molecular and biological data on older adults receiving acute care. This study included patients who were recruited until 2019. Potential participants were screened for eligibility after they were provided with information describing the study. Eligibility criteria included: age ≥ 65 years, admission to one of the INRCA research hospitals, and written informed consent. In the case of a participant's cognitive decline or impaired judgment, a proxy (relative or caregiver) was requested to give their additional consent. The absence of informed consent from the patient or caregiver (50) resulted in the participant's exclusion from the study. Baseline data were collected for each patient within the first 24 h of hospital admission. Baseline data were incorporated into a minimum data set comprising demographic information, multidimensional geriatric assessment data, clinical, biological, and diagnostic information routinely collected during hospitalization, also utilizing the interRAI Acute Care Instrument (51). Moreover, the Reportage dataset contained information on drug intake (prior to admission, during hospitalization, and at discharge) and diagnostic and treatment procedures performed during hospitalization (including information from X-rays, computerized tomography, ultrasounds, electrocardiograms, magnetic resonance imaging, etc.). The multidimensional geriatric assessment was repeated within 24 h prior to discharge. Blood samples were taken within 24 h of admission and stored at −80°C. A separate and detailed data sheet was used to collect data regarding *ad hoc* investigations to identify biological markers.

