### Phase II: Patient selection

One thousand and seventy hospitalized older adults will be randomly selected from the Reportage database on the basis of the following inclusion criteria:

- Age ≥ 65 years.- Clinical records: two or more of the following conditions on an ongoing basis (present in at least 5% of the overall population): heart attack/myocardial infarction, cerebrovascular disease (CVD), dementia, chronic kidney disease (CKD), hypertension, dyslipidemia, ischemic cardiomyopathy, stroke, PAD, chronic obstructive pulmonary disease (COPD), diabetes, cancer, Parkinson's disease, heart failure, atrial fibrillation, anemia, deafness, hip fracture, thyroid dysfunction, asthma, depression, migraine, eczema/dermatitis, irritable bowel syndrome, osteoporosis, anxiety/panic attacks, rheumatoid arthritis, glaucoma, ear/vestibular disorders, epilepsy, chronic sinusitis, tuberculosis, meningitis, multiple sclerosis, bronchiectasis, prostate problems, schizophrenia, hepatitis, liver failure/cirrhosis, and inflammatory bowel disease.- Availability of blood and plasma samples at the IRCCS-INRCA: buffy coat and plasma samples (withdrawn at baseline) stored at −80°C.- Availability of information from baseline to 10 years of follow-up: death, hospitalization, clinical records, functional status, routine laboratory parameters, onset of new comorbidities after the first discharge, and drug intake.

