#### Clinical variables

The objective examination includes blood pressure, heart rate, and anthropometric variables (body mass index, BMI). A thorough clinical history was carefully compiled by trained physicians. Diagnoses were coded using the International Classification of Diseases, 10^th^ Edition (ICD10) (54) and the coding of medications was carried out by means of the Anatomical Therapeutical Chemical Classification System (ATC) (55).

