### Statistical analysis

Baseline characteristics will be described using standard descriptive methods, such as summary statistics and frequency tables. Parametric and non-parametric statistical approaches (such as contingency table analysis, regression, and analysis of variance) will be used when appropriate.

Data pre-processing will be performed using the R package *minfi* (56) and a DNA methylation level will be summarized for each CpG site by calculating a “*beta*” value ranging from 0 to 100%. CpG probes will be treated as missing if the detection *P*-value > 0.01, and CpG sites with more than 5% missing data will be excluded from the analysis.

Epigenetic age will be calculated by multiplying beta values by the regression weights from Horvath [353 CpG sites (35)], Hannum [71 CpG sites (37)], and Levine [513 CpG sites (38)] to create the respective clocks. Delta age (Δage) will be defined as a simple subtraction of the chronological age from the epigenetic age using all the versions of the clock mentioned previously. In all cohorts, cell count predictions will be estimated from DNA methylation data using the Houseman method (57).

The determinants of overall 10-year survival will be calculated using Cox proportional hazards analysis including Δage as independent variables, and corrected for the following confounders: age, gender, clinical, functional, or biological data. The accuracy of exposure variables in predicting mortality will be estimated using Harrell's C-statistics. The same analyses will be repeated by adding the individual age-associated CpGs (one at once) to the Cox model. A two-stage approach will be adopted to validate individual CpG sites associated with mortality. Initially, all of the more than 850,000 methylation sites analyzed by the Illumina Infinium MethylationEPIC Array will be analyzed in a proportion π_sample_=25% of the study sample in stage 1 (*n* = 272), and the results of stage 1 will be used to select a proportion of these *M* CpG sites (Ω_marker_) for follow-up on the remaining sample in stage 2 (75%, n=798). The parameter Ω_marker_ will be selected on the basis of the corresponding *p*-values within the context of the survival analysis.

The validity of the estimated coefficients will be internally verified using a non-parametric bootstrapping resampling analysis with replacements.

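### Δage is read from leukocyte DNA but blood cancers are not set aside: a few such samples could create or mask the Cox association, by an amount the protocol does not let one size

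*Protocol article*

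**What the plan says.** All places are in the protocol article.

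- **Phase II: Patient selection.** Two or more listed conditions make a patient eligible. The list includes "chronic obstructive pulmonary disease (COPD), diabetes, cancer", with no sub-type. The qualifier "present in at least 5% of the overall population" refers to the listed conditions and says nothing about blood cancers separately.
- **Study design.** The only exclusion stated for the parent cohort is "The absence of informed consent from the patient or caregiver".
- **Phase IIIb** and **Epigenetic variables.** The tissue is buffy coat: "DNA is extracted and purified from frozen buffy coat samples for each selected individual".
- **Statistical analysis.** Δage "will be defined as a simple subtraction of the chronological age from the epigenetic age". It enters a Cox model with age, gender and unspecified clinical, functional or biological data as confounders. On cell composition, "cell count predictions will be estimated from DNA methylation data using the Houseman method"; the text does not say that these estimates enter the Cox model. CpG sites are selected by their survival p-values in stage 1 (n = 272) and followed up in stage 2 (n = 798).
- **Clinical variables.** "Diagnoses were coded using the International Classification of Diseases", 10th edition, so the information needed to recognise blood cancers is already held.

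**The concern.** Buffy coat is the leukocyte layer. In leukaemia, or lymphoma with circulating cells, part of the DNA on the array comes from the tumour, and the resulting Δage is not a clean measure of the patient's own epigenetic ageing. The stated criteria admit such patients.

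The safeguards in the text help only in part:

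- Houseman estimates describe normal leukocyte types, not a malignant clone.
- One cancer indicator pools these patients with the solid tumours.
- The bootstrap resamples the same affected patients.
- The random 25%/75% split puts such patients in both stages, so stage 2 can repeat an artefact from stage 1.
- The risk analysis is repeated within each multimorbidity pattern, and Strengths and limitations names cancer as a pattern. Affected samples would gather there.

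At stake is the Cox coefficient for Δage. Outlying values joined to high mortality could produce an association where none exists, or pull a real one towards zero.

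**Working it through.** **1. The plan's own figure.** Inputs from Sample size: α = 0.05, power 80%, HR 1.23, 10 years, reference median 6.2 years; two-sided from Statistical analysis. An equal split and exponential survival are assumed.

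- Deaths needed (Schoenfeld): 4 × (1.960 + 0.842)² / (ln 1.23)² = 733. Freedman's formula gives 738.
- 10-year death probability: 1 − 2^(−10/6.2) = 0.673 in the reference group and 0.747 at HR 1.23; mean 0.710.
- N: 733/0.710 = 1,032 to 738/0.673 = 1,097. The stated 1,070 lies in this range and is not in dispute.

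**2. Inputs not in the documents (all assumed).** Δage SD 6 years; 5, 10 or 20 affected of 1,070 (2 or 5 of 272); shift +20, +40 or −30 years; mortality HR 2 or 4. On this scale +40 years is 40/6 = 6.7 SD and −30 years is −5 SD, which is why a few patients carry leverage.

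**3. Model.** Death rate ln 2/6.2 per year times the hazard ratios, censoring at 10 years. Observed Δage = true Δage + shift in affected patients. Cox regression on Δage/6, significant if |z| > 1.96; 1,500 runs per setting, 400 in steps 4 and 5. Both sample sizes are shown because the array is run on 272 in stage 1 while Sample size plans the association on 1,070.

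| Setting, no cancer covariate | Affected | P(p < 0.05) |
|---|---|---|
| N = 1,070, no true effect | 5 | 5–14% |
| | 10 | 10–40% |
| | 20 | 18–90% |
| N = 1,070, true HR 1.11 per SD | 0 | 81% |
| same, shift −30 | 5 | 51–63% |
| | 10 | 27–45% |
| | 20 | 5–17% |
| N = 272, no true effect | 2 | 6–10% |
| | 5 | 9–34% |

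The spurious HR per SD in the whole cohort reaches at most 1.03, 1.06 and 1.10 with 5, 10 and 20 patients, and falls as low as 0.92 with a negative shift.

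**4. With a yes/no cancer covariate** (160 of 1,070 with cancer, cancer HR 2), no true effect, +40 years: 8% with 5 patients (HR 4), 7–17% with 10 (HR 2–4), 41% with 20 (HR 4). With a true HR of 1.11 and 5 patients at −30 years, power is 64–77% against 84% without them.

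**5. Within a cancer pattern of 160.** Five patients (+40 years, HR 4) give 49% false positives. Five at −30 years (HR 2) reduce a true HR of 1.23 to 1.08.

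**6. Harrell's C.** In the whole cohort it moves by about 0.01 or less; the largest change, with 20 patients (+40 years, HR 4), is from 0.5015 to 0.5128. In the cancer pattern, 5 such patients move it from 0.5047 to 0.5244. With Δage split at the median in the whole cohort, false positives stay at 5–10%.

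**7. How far the result depends on the assumptions.** A second set of runs assumed solid tumours in 17% (HR 1.7) and no true effect. Entries are unadjusted / adjusted for any cancer.

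| Blood cancer | n = 272 | n = 1,070 |
|---|---|---|
| 3%, all shifted +30 years, HR 3 | 33% / 14% | 85% / 42% |
| 3%, only 30% of them shifted +30 years, HR 3 | 7% / 5% | 20% / 10% |
| 1%, all shifted +30 years, HR 3 | 10% / 5–8% | 20–26% / 10–13% |
| 2%, all shifted +15 years, HR 2 | 6% / 4% | 12% / 6% |
| 1% all shifted, or 3% with 30% shifted; +15 years, HR 2 | 4–6% | 4–6% |

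Repeat runs of the first row gave 30–32% / 11–14% and 81–82% / 38–41%. Leaving out the affected patients returned the rate to 4–7% in every setting tried. Fitting separate blood-cancer and solid-tumour terms gave 4%.

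**The case against.** The article condenses a fuller approved protocol that is not shown, and sample-level exclusions or sensitivity analyses may stand there. Every decisive input is assumed, including the direction of the shift. The largest figures shift every blood-cancer patient, although the mechanism needs malignant cells in the baseline sample. The plan also adjusts for clinical data, considers multiple covariates, applies Bonferroni and judges accuracy by Harrell's C.

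Much of this stands. The size cannot be fixed from the documents, and a separate blood-cancer term would largely remove the false positives. But the text names no such term. Bonferroni over three clocks lowers the nominal level to 0.05/3 = 1.7%; the cancer-adjusted rates in the 3%, +30 years, HR 3 setting are then 8% (n = 272) and 25% (n = 1,070), still above it. The bootstrap can reveal instability but does not remove a systematic effect.

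It is also right that listing cancer is not the only route in: a patient with blood cancer can qualify on two other conditions. The gap is therefore the missing rule for these samples, not the presence of cancer on the list. And an exclusion of all past blood cancer would go further than the mechanism requires.

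A reader might infer that a few such patients will by themselves produce the clock's association with death. The documents do not support that: they give no count, shift or mortality for these patients, and five of 1,070 barely raise the false-positive rate in most settings.

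**Conclusion.** The gap is certain from the stated criteria; its size is conditional. For continuous Δage in the Cox model the effect runs from negligible (few patients, +15 years, HR 2, or only a minority shifted) to material. In the whole cohort, creating an association takes about 10–20 or more of 1,070 with large shifts; within a cancer pattern of 160, about 5 are enough. Masking needs fewer: 5 of 1,070 at −30 years cut 81% power to 51–63% without a cancer covariate. Harrell's C in the whole cohort is largely unaffected. No computation was made for the CpG selection; there the argument is qualitative.

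It would be too strong to call the primary analysis invalid or the sample size wrong. This is a cheap improvement worth making before the methylation data are analysed. All magnitudes rest on the assumed SD of 6 years and the assumed counts, shifts and hazard ratios.

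**What to change.** Use the ICD-10 codes already recorded to flag haematological malignancy that is ongoing at the baseline blood sample. Then pre-specify that:

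1. flagged patients are left out of the Δage Cox model and the CpG selection, and are replaced by further random selection if the arrays have not been run;
2. they stay in the analyses of clinical data;
3. the Cox model is reported with and without them.

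**Cost.** A code query, a sentence in Phase II and one extra model. Without replacement, losing 20 patients leaves 1,050 × 0.710 ≈ 746 deaths. Power is Φ(√(746/4) × 0.207 − 1.960) = 0.807, against 0.814 at 1,070, a loss of under one point. Replacement keeps 1,070. The clock result would generalise slightly less widely, because it would no longer cover patients with active blood cancer.

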### Phase IVa: Epigenetics analyses in 25% of the whole sample (stage 1)

Epigenetic analyses on the PROMOTERA project will be divided into two stages: in stage 1, genome-wide methylation profiles, obtained by utilizing the Illumina Infinium MethylationEPIC Array, will be determined as a proportion π_sample_ = 25% (*n* = 272) of the overall PROMOTERA study sample. This population will be selected at random. Stage 1 results will be used to choose a proportion of the *M* CpG sites (Ω_marker_) that are strongly associated with primary and secondary outcomes.

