### Objectives

#### Primary objective

The main objective of this study is to evaluate the performance of the epigenetic clock expressed as *epigenetic age acceleration (epigenetic clock age–chronological age)* in predicting all-cause mortality in a cohort of MM older patients.

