### Phase V: Validation of biomarkers in the entire study population (stage 2)

The biomarkers selected in phases IVa and IVb will be validated on the remaining samples (75%, *n* = 798).

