In order to reduce the complexity of MM, a dimensionality reduction approach will be performed by clustering patients into a few groups on the basis of the most frequent diagnoses at baseline for each stratum in order to obtain a classification of patients according to an MM pattern. The risk analysis will be repeated for each MM pattern. The association between the epigenetic clock and MM patterns will be determined by means of a Generalized Linear Model. Multiple adjusted models will be developed to consider each possible covariate that could influence the significance of the results and to identify independent variables linked to primary and secondary outcomes. Survival analysis with Kaplan Meier estimates will be performed to assess and compare survival over time among the clusters (Log-Rank test). Cox proportional hazards models will be used to assess and compare survival-time outcomes in each cluster in the presence of possible confounders. Several network medicine-based approaches will be developed in order to build the Human Interactomes and Disease Networks (58). Finally, we will investigate the additive effect of the epigenetic clock on the predictive ability of MM patterns. Changes in Harrell's C and the categorical Net Reclassification Index (NRI) will be calculated with 1,000 bootstrap samples to estimate the 95% CI. A two-tailed *p*-value of < 0.05 will be considered statistically significant. The Bonferroni correction for multiple comparisons will be applied to control for the risk of false-positive results. Statistical analyses will be conducted using the Stata 15.1 Software Package for Windows (Stata Corp, College Station, TX).

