### Sample size

The sample size was calculated on the basis of the primary objective (the association between the epigenetic clocks' Δage and mortality). For this reason, we planned to include 1,070 samples of individuals from the Reportage Project. This sample was obtained by setting α = 0.05, β = 0.2, and using a Hazard ratio = 1.23, a 10-year follow-up period, and a median survival time of 6.2 years for patients whose Δage was not expected to increase. This sample size is also in line with other study populations in which the prognostic value of several epigenetic clocks were assessed (36). This sample will enable the detection of significant associations between epigenetic clock Δage and mortality during the 10-year follow-up period.

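### As written, nothing provides the clock CpG sites in the 798 stage-2 patients, yet the sample size rests on Δage in all 1,070; if only 272 have Δage, power for HR 1.23 is about 30%

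*Protocol article*

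**What the plan says.** All references are to the protocol article.

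- **Primary objective:** to "evaluate the performance of the epigenetic clock expressed as" epigenetic minus chronological age (Δage), as a predictor of all-cause mortality.
- **Sample size:** "The sample size was calculated on the basis of the primary objective". Then: "For this reason, we planned to include 1,070 samples of individuals from the Reportage Project". The inputs: "This sample was obtained by setting α = 0.05, β = 0.2, and using a Hazard ratio = 1.23", with 10 years of follow-up and a median survival of 6.2 years in the reference patients.
- **Phase IVa (stage 1):** "genome-wide methylation profiles, obtained by utilizing the Illumina Infinium MethylationEPIC Array, will be determined as a proportion" of 25%, n = 272, chosen at random.
- **Phase V (stage 2):** "The biomarkers selected in phases IVa and IVb will be validated on the remaining samples", that is 75%, n = 798.
- **Statistical analysis:** "Epigenetic age will be calculated by multiplying beta values by the regression weights from Horvath" (353 sites), and likewise from Hannum (71) and Levine (513). The CpG sites that go forward to stage 2 are chosen by their p-values in the survival analysis.

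Three places suggest wider measurement. The abstract speaks of thousands of CpG sites in a sample of 1,070. The section on epigenetic variables names the array without limiting it to stage 1. The statistical section says that cell counts will be estimated from methylation data in every cohort.

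**The concern.** Each clock is a weighted sum over a list of sites fixed in advance. A patient has a Δage only if those sites have been measured. The sections that say who receives which assay give the array to 272 patients. They give the other 798 only what stage 1 selects, and CpG sites are selected by their own association with survival, not by membership of a clock. No section carries the clock sites forward. Followed literally, the plan does not provide the primary exposure for three quarters of the sample (798/1,070 = 74.6%), although the sample size was justified by that exposure in all 1,070.

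If the study ran that way, the stated 80% power would not apply to the primary analysis, and a null result on Δage would say little.

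**Working it through.** **Inputs.** Sample size section: two-group description (a reference group whose Δage is not expected to increase), α = 0.05, power 80%, HR 1.23, 10 years, reference median 6.2 years. Statistical analysis section: "A two-tailed *p*-value of < 0.05 will be considered statistically significant", hence two-sided. Assumed because not stated: exponential survival, equal groups, everyone followed for 10 years.

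**Step 1. Death probabilities.**
- Reference hazard = ln 2 / 6.2 = 0.1118 per year; 10-year risk = 1 − exp(−1.118) = 0.673.
- With HR 1.23: 1 − exp(−1.118 × 1.23) = 0.747.
- Mean of the two groups: 0.710.

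**Step 2. Reproduce 1,070.**
- Schoenfeld: events = 4 × (1.96 + 0.842)² / (ln 1.23)² = 733, so N is about 733 / 0.710 = 1,032.
- Freedman: events = (1.96 + 0.842)² × (2.23 / 0.23)² = 738, so N is about 1,040.
- Both are within about 4% of 1,070. One-sided testing gives 814 to 820 and does not fit.
- At 1,070: 1,070 × 0.710 = 760 deaths; power = Φ(0.207 × √(760/4) − 1.96) = 81%.

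The plan's figure is therefore, to a close approximation, a two-group calculation with Δage known in everyone.

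**Step 3. Same inputs, n = 272.**
- Deaths: 272 × 0.710 = 193.
- Power = Φ(0.207 × √(193/4) − 1.96) = Φ(−0.52) = 30%.
- HR detectable with 80% power = exp(2 × 2.802 / √193) = 1.50.

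**Step 4. Sensitivity at n = 272.**

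| Assumption | Power for HR 1.23 |
|---|---|
| Equal groups, all followed 10 years | 30% |
| 40/60 split | 29% |
| 25/75 split | 23% |
| Equal groups, uniform entry over 8 years within 10 years in total | 23% |
| Continuous normal Δage whose median-split HR is 1.23 | 44% |
| Equal groups, every patient dies | 40% |

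**Step 5. The per-SD reading.** If HR 1.23 were per standard deviation of a continuous Δage, events needed = (2.802)² / (ln 1.23)² = 183. That is 183 / 0.710 = 258 patients, or 183 / 0.673 = 272 if the reference risk is used. Power at 272 would then be about 80%. This reading does not lead to 1,070.

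**The case against.** The strongest reply is that the article never says Δage is limited to 272. The statistical section describes the Δage Cox model first, and introduces the two-stage approach afterwards as a way to validate individual CpG sites. On that reading the p-value filter concerns discovery only, and the clocks, whose sites need no selection, stand outside it. Phase IIIb extracts DNA from every selected patient, and the abstract, the epigenetic variables section and the remark on cell counts fit methylation data in all 1,070. The stage-2 assay is not described at all, which a condensed article may leave to the full protocol.

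Much of this stands. It rules out the flat statement that Δage will exist in only 272 patients. It does not remove the conflict. Phase IVa divides the project's epigenetic analyses as a whole into two stages, Phase V gives the 798 only selected biomarkers, and no sentence says that the array or the clock sites are run in them. The article itself fixes both the sample size and the division of assays, so this is more than omitted detail.

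A second reply is the per-SD reading, under which 272 patients would suffice. The match with 272 is striking, since a quarter of 1,070 is 267.5, but the article does not say that 272 was derived this way. It says its inputs produced 1,070, and it describes a reference group. If per SD was meant, 1,070 does not follow from those inputs.

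Two further inferences are tempting but unsupported. One is that most clock sites would fail the stage-1 filter: no threshold is given, so this cannot be judged. The other is that power falls further through a Bonferroni correction over the three clocks: the limitations section ties the correction to the number of modifiers tested, and the general statement in the statistical section does not mention the clocks.

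**Conclusion.** The point holds as an unresolved conflict over the primary exposure. The sections that allocate assays do not provide Δage in 798 of 1,070 patients, while the sample size section requires it in all of them. A reader might conclude that the true power is 30% and not 80%. The documents do not support that as a fact, because other wording points to wider measurement; if the clock sites are measured in all 1,070, power is about 81% and the problem disappears.

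If Δage is confined to stage 1, power for HR 1.23 is about 30%, with a detectable HR of about 1.50. This assumes equal groups, exponential survival and complete 10-year follow-up. The alternatives examined, other than the per-SD reading, run from about 23% to 44%, so none comes near 80%. Because the per-SD reading gives a different answer, the missing scale of the HR is part of the same problem.

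**What to change.** Reconcile Phase IVa, Phase V, Statistical analysis and Sample size in one of two ways.

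1. **Δage in everyone.** State in Phase IVa, Phase V and Statistical analysis that the Horvath, Hannum and Levine sites (353 + 71 + 513 = at most 937) are measured in all 1,070 patients regardless of stage-1 p-values, by the array or by a stage-2 assay able to carry them. If this was always intended, the cost is a sentence. If not, the cost depends on an assay that the article does not specify and could be substantial for 798 further samples. It has to be settled before the stage-2 assay is run.
2. **Δage in stage 1 only.** State under Sample size that the primary analysis uses n = 272, with about 193 expected deaths, about 30% power for HR 1.23 under equal groups (with the range above), and a detectable HR of about 1.50. This costs only wording, but the figure is much less favourable.

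In either case, state under Sample size whether HR 1.23 compares two groups, and in what proportions, or is per unit or per SD of Δage.
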